#### Primary outcomes

The primary outcome in this study is glycosylated hemoglobin (HbA1c), which means the comparison of HbA1c change between two groups after 12 weeks of intervention. HbA1c is a critical indicator for the diagnosis of T2DM, which can reflect average levels of glycemia during the preceding 3 months and is widely used for diabetic complication assessment [28]. It is considered the gold standard for predicting glycemia-associated risks for the microvascular and macrovascular complications of diabetes mellitus over 5–10 years [29]. Therefore, the value of HbA1c in the care of patients with T1DM and T2DM is unassailable [30]. Professional societies, public health organizations, regulatory agencies, patients, and clinicians have focused on HbA1c levels to gauge the quality of diabetes care, and over time, HbA1c level has supplanted other indicators of the quality of diabetes care, such as blood glucose levels and symptoms of hyperglycemia, despite being a surrogate rather than a direct marker of glycemic control [31]. In addition, careful regulation of blood glucose concentrations in patients with diabetes mellitus normalized HbA1c over 6 weeks [32], so it has also excellent reliability and validity and is sensitive enough for clinical and research practice.

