### Statistical analysis

SPSS 20.0 software was used for the statistical analysis of data. Measurement data were described as mean (M) ± standard deviation (SD). Normality of continuous data was evaluated using the Kolmogorov–Smirnov test and Q–Q plot. If the paired samples were in accordance with normal distribution, the *t*-test of the paired samples was used for pairwise comparison. If not, the nonparametric test was adopted. If the two independent samples were in accordance with the normal distribution and homogeneity test of variances, the *t*-test of the independent sample was used. The *t*'-test was used when the variance was not in uniform and the nonparametric test was adopted when the samples were not in accordance with normal distribution. The covariance analysis will be performed regardless of the comparability in the baseline of Hba1c values of the two groups before treatment. Enumeration data like gender and medical history was described statistically by frequency. The chi-square test and Wilcoxon rank sum test were used to determine whether there was comparability between the two groups. All statistical tests are bilateral, and a *P* value ≤ 0.05 would be considered statistically significant.

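### Two different analyses apply to the primary HbA1c comparison and the plan does not say which one decides, so the 5% error rate is not protected and power depends on an unstated choice

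*Protocol article*

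**What the plan says.** The protocol article, Primary outcomes, defines the endpoint as "the comparison of HbA1c change between two groups after 12 weeks of intervention". It does not attach a test to it.

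The Statistical analysis section then contains two instructions that both reach this comparison.

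- A general rule for continuous data. The gate is set first: "Normality of continuous data was evaluated using the Kolmogorov–Smirnov test and Q–Q plot". The t-test follows "If the two independent samples were in accordance with the normal distribution and homogeneity test of variances". A t'-test is used if the variances differ, and "the nonparametric test was adopted when the samples were not in accordance with normal distribution". The rule does not except HbA1c.
- An unconditional rule that names HbA1c: "The covariance analysis will be performed regardless of the comparability in the baseline of Hba1c values of the two groups before treatment". It states neither the dependent variable nor whether the result is primary or supportive.

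The same section also provides for paired tests, beginning "If the paired samples were in accordance with normal distribution". One threshold covers everything: "All statistical tests are bilateral", and a P "value ≤ 0.05 would be considered statistically significant".

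**The concern.** A trial with one primary outcome needs one deciding analysis, fixed before the data are seen. Here two analyses of the same contrast can give different answers, and the text ranks neither above the other. Two things are at stake.

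- **Error rate.** If the choice is left open until both P values are known, or if either is accepted, there are two correlated chances of a false positive.
- **Power.** The two analyses are not equally efficient. An unadjusted test on change carries the full noise of the baseline measurement, whereas covariance analysis removes what baseline predicts. With 30 per arm the difference can be material.

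**Working it through.** **Inputs.** From Sample size: 30 per arm, 0.65-SD difference, 80% power, α 0.05, 15% dropout. From Statistical analysis: two-sided tests. Assumed: the correlation r between baseline and week-12 HbA1c is not given, so 0.3 to 0.8 is shown. The 0.65 SD is taken as the SD of the HbA1c value, with equal SD at both visits.

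**The plan's own figure.** For an unadjusted two-sided comparison, n per arm = 2(1.960 + 0.842)²/0.65² = 37.2, so 38 (39 with the exact t distribution), or 45–46 after 15% dropout. The stated 30 is not reproduced, and 30 per arm gives 70% power. That is a separate sample-size matter. It is used here only as the reference point for the comparison below.

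**Power by closed form.** In units of the HbA1c SD, the SD of change is √(2(1−r)) and the residual SD after covariance adjustment is √(1−r²). The standardised effect is 0.65 divided by that SD. The noncentrality is this effect × √(30/2), on 58 degrees of freedom for change and 57 for covariance analysis.

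| r | SD of change | Residual SD | Noncentrality, change | Noncentrality, ANCOVA | Power, change | Power, ANCOVA |
|---|---|---|---|---|---|---|
| 0.3 | 1.183 | 0.954 | 2.13 | 2.64 | 0.55 | 0.74 |
| 0.5 | 1.000 | 0.866 | 2.52 | 2.91 | 0.70 | 0.81 |
| 0.7 | 0.775 | 0.714 | 3.25 | 3.53 | 0.89 | 0.93 |
| 0.8 | 0.632 | 0.600 | 3.98 | 4.20 | 0.97 | 0.98 |

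**Power by simulation with the gates applied.** The procedure was Kolmogorov–Smirnov with the Lilliefors correction, then Levene, then t, Welch or Mann–Whitney on change, with 40,000 trials per setting and normal data. For r = 0.3 / 0.5 / 0.7 / 0.8:

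- 30 per arm: pretest route 0.54 / 0.69 / 0.89 / 0.97; ANCOVA 0.73 / 0.81 / 0.93 / 0.98.
- 25 per arm (about 30 less 15%): pretest route 0.48 / 0.62 / 0.83 / 0.95; ANCOVA 0.65 / 0.73 / 0.88 / 0.96.

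A separate run of 3,000 trials per cell with 30 per arm gave 55% v 72%, 69% v 80%, 89% v 93% and 97% v 98%. Across these runs the loss with 30 per arm is about 17–18, 11–12, 4 and 1 points.

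**How often the choice matters.** The proportion of trials in which exactly one analysis is significant is 2 × P(either) − P(pretest route) − P(ANCOVA). With a true 0.65-SD effect and 30 per arm:

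- r = 0.3: 2 × 0.758 − 0.543 − 0.728 = 24%
- r = 0.5: 2 × 0.833 − 0.690 − 0.808 = 17%
- r = 0.7: 2 × 0.943 − 0.891 − 0.931 = 6%
- r = 0.8: 2 × 0.986 − 0.974 − 0.984 = about 1.5%

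**Type I error (no true effect; normal and skewed errors; 25 and 30 per arm).**

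- Pretest route alone: 4.9–5.4%.
- ANCOVA alone: 4.7–5.1%.
- Significance on either, with the unadjusted test on change: 6.6–8.1%. If the unadjusted test were run on week-12 values instead, the range would be 6.4–9.0%.

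**The case against.** The strongest reply is that the plan already has a single analysis for HbA1c. The t, t' and rank rules are generic and never name it. The covariance sentence is the only analysis sentence that does, and it is unconditional. A specific rule for the primary variable alongside a general rule for the rest is a natural reading. It stands as plausible, but the text does not say it: HbA1c is not taken out of the general rule and the covariance analysis is given no role.

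A second reply is that ranking analyses belongs in a statistical analysis plan, which is not shown. That would answer an omission. Here the article itself prescribes two analyses of one comparison under one threshold.

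A third is that the power loss is conditional. That stands: it needs the unadjusted test to decide, and it is negligible at r = 0.8. If the 0.65 SD is instead the SD of change, the unadjusted power is about 0.70 whatever r is. ANCOVA then has effect 0.65 × √(2(1−r))/√(1−r²), that is 0.81, 0.75, 0.71 and 0.68, and power of about 0.87, 0.81, 0.77 and 0.74. The direction is unchanged.

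Some stronger readings are tempting and are not supported.

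- A reader might infer that the plan breaches the 5% level. It does not as written: each route alone holds about 5%, and no sentence sets a rule that either may win.
- A reader might fault the normality gate as such. It does not inflate the error in these simulations, and nothing in the document ties HbA1c to a markedly skewed distribution.
- A reader might argue that HbA1c could still be moving after a one-week run-in, or that a within-arm change could be taken as efficacy. Movement common to both arms cancels between groups, the primary outcome is defined as a between-group comparison, and neither point bears on which between-group test decides.

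**Conclusion.** The concern holds in limited form. Two analyses reach the primary comparison and the deciding one is not named. The 5% rate is therefore unprotected rather than broken: about 5% under either analysis fixed in advance, about 7–8% if either may count. If the unadjusted test on change decides, the power given up at 30 per arm is about 17 points at r = 0.3, 11 at r = 0.5, 4 at r = 0.7 and 1 at r = 0.8. These figures rest on an assumed r, on 0.65 SD being the SD of the HbA1c value and, for power, on normal data. The type I error range also covers skewed errors. This concerns the trial's one confirmatory comparison and cannot credibly be settled once results by arm are known.

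**What to change.** State in Statistical analysis that the single primary test is a covariance analysis of week-12 HbA1c (or of change) on treatment arm with baseline HbA1c as covariate, two-sided at 5%, with no normality or variance gate in front of it. Label the t, t' and rank results for HbA1c as supportive and the paired within-arm tests as descriptive. Use the same baseline-adjusted model for the continuous secondary outcomes measured at both baseline and week 12, such as fasting and postprandial glucose, insulin, C-peptide and the inflammatory factors.

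Fixed this way, simulated type I error is 4.7–5.1%. The cost is analysis wording only: Table 1 already schedules HbA1c at baseline and week 12. The change should be made before any outcome data are analysed by arm.

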**Methods and analysis:**

This trial is a randomized, double-blind, placebo-controlled study. A total of 60 participants will be randomized in a 1:1 ratio into an experiment group (RG formula) and a control group (placebo). Patients in both groups will be given diabetes education and basic blood glucose control. Glucose-lowering drugs with significant influence on gut microbiota will be avoided. This trial will last 25 weeks including 1-week run-in, 12-week intervention, and 12-week follow-up visit. The primary outcome is the change in the HbA1c. The secondary outcomes comprise the change in the fasting blood glucose (FBG), postprandial blood glucose (PBG), fasting insulin (FIL), fasting C-peptide(C-P), insulin resistance index (IRI), inflammatory factors, and species abundance of gut microbiota between the two groups. Safety of medication will also be evaluated. The correlation analysis will be explored between the glycemic indicators, inflammatory factors, and abundance of gut microbiota.

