Previous studies found that the formula of Coptis root and ginseng (RG) could reduce postprandial blood glucose by inhibiting intestinal α-glucosidase in T2DM patients [23]. Our team also demonstrated that the RG formula could alleviate insulin resistance in diabetic rats through inhibiting the expressions of pro-inflammatory factors and pro-apoptotic factors in pancreatic islets, up-regulating adiponectin receptors, and reducing the level of serum-free fatty acids [24, 25]. Whether long-term intervention of RG formula will remodel the structure of gut microbiota, reduce inflammation, and improve insulin resistance is worthy to be explored. Based on the viewpoint of gut microbiota, this study aims to (1) assess the clinical efficacy of RG formula in adults with T2DM, (2) characterize the influence of RG formula on levels of inflammatory cytokines and structural changes of gut microbiota, and (3) analyze the relationship between changes in gut microbiota, inflammatory cytokines, and clinical assessments, in order to demonstrate the underlying mechanism of TCM treatment in T2DM patients.

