
### Outcome measures

The physical condition of patients should be recorded at baseline, week 4, week 8, and week 12.

At the start of the trial, patient’s general information including name, gender, age, education, marriage condition, BMI, etc., will be collected. The complications of diabetes such as diabetic retinopathy, diabetic nephropathy, diabetic peripheral neuropathy, and diabetic peripheral vascular disease should be noted. Other diseases and their corresponding treatment, symptoms, tongue and pulse condition of TCM should also be collected. At week 4 and week 8, two follow-up visits are conducted to collect TCM-related indicators such as symptoms, tongue signs, pulse signs, and symptom diagnosis. At week 0 and week 12, fecal samples and blood samples are collected for quantitative determination of gut microbiota, serum biochemical indicators, and inflammatory indicators.

Stool sample measuring is based on the 16S rRNA sequencing technology of microbiome. It will detect qualified environmental microbial DNA extraction and make the PCR amplification for the general area in V3-V4 primer in DNA base sequence of the designated areas. After a large number of replicated increments, the result will be compared to the existing databank. When the sample passes the inspection, DNA data will be uploaded to Illumina Hiseq 2500 high-throughput sequencing platform for OTU annotation and relative abundance analysis, so as to calculate the species abundance of all samples at phylum, class, order, family, and genus levels. On the basis of these results, the clustering of species abundance, association analysis of common specific OTU, and inter-group differential species analysis will be completed.

Measures of blood samples are divided into biochemical index and inflammation index. As for biochemical index, FBG and PBG are measured by hexokinase method, HbA1c by glycosylated hemoglobin automatic analyzer using the ion-exchange HPLC method, insulin and C peptide by the chemiluminescence method, urea by the colorimetric method, creatinine values by the sarcosine oxidase method, and ALT and AST by the rate method. As for inflammatory indicators, IL-6, TNF-α, and CRP are determined by professional operators using relevant detection kits and enzyme-labeled analyzer (Infinite F50).

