#### Secondary outcomes

The secondary outcomes are mean changes in FBG, PBG, FIL, C-P, IRI, inflammatory factors, and species abundance of gut microbiota. FBG, PBG, FIL, and C-P will be measured to further assess the status of insulin resistance. PBG is obtained by rapid detection of fingertip blood. FBG, FIL, and C-P are obtained by venous blood sample which will be collected after an overnight by a trained medical officer/investigator and transported to a standard laboratory for analysis. Laboratory technicians are blinded to the study participants. The insulin resistance index of the homeostasis model is based on the formula developed by Matthews [33]. The inflammatory factors include interleukin-6 (IL-6), tumor necrosis factor α (TNF-α), and C-reactive protein (CRP). The species abundance of gut microbiota will be based on the second-generation high-throughput sequencing technology.

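### The blanket unadjusted P ≤ 0.05 rule, read literally, leaves the gut-microbiota comparisons and their correlations with clinical markers without control of false positives

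*Protocol article*

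**What the plan says.** The closing sentence of the Statistical analysis section has two parts. The first fixes scope and sidedness: "All statistical tests are bilateral". The second fixes the threshold: a P "value ≤ 0.05 would be considered statistically significant". No other section adjusts this threshold or exempts any analysis from it.

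Three other places show what the sentence reaches.

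- **Secondary outcomes** makes microbiota abundance a formal endpoint: "The secondary outcomes are mean changes in FBG, PBG, FIL, C-P, IRI, inflammatory factors, and species abundance of gut microbiota".
- **Outcome measures** describes 16S sequencing, processed "so as to calculate the species abundance of all samples at phylum, class, order, family, and genus levels". It then plans a comparison of taxa between the groups. It names no taxa and gives no level, test or threshold for that comparison.
- **Abstract, Methods and analysis** adds: "The correlation analysis will be explored between the glycemic indicators, inflammatory factors, and abundance of gut microbiota".

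The tone is mixed. The Abstract speaks of exploring the correlations, whereas the Background gives the purpose of the aims as "in order to demonstrate the underlying mechanism of TCM treatment in T2DM patients".

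**The concern.** This is a stated rule and not a gap left for a statistical analysis plan. A plan that adjusted for multiplicity would have to override the sentence.

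Under the rule, a screen over many taxa chosen by no prior hypothesis has the same threshold as the single primary comparison. Some taxa will cross 0.05 by chance, and the rule calls each of them significant. The same holds, on a larger scale, for a grid of taxa against clinical markers. The second and third aims (microbiota and cytokine changes, and their relation to clinical measures) rest largely on these results. If the correlations are then offered as showing how the formula works, chance findings could be reported as mechanism.

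**Working it through.** The plan has no figure of its own to reproduce here: it states the threshold but neither the number of tests nor an expected error rate. The check therefore asks what the threshold implies over a range of test counts.

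**Inputs from the protocol article**
- Threshold 0.05, two-sided, all tests (Statistical analysis).
- Five taxonomic levels, taxa not counted or named (Outcome measures).
- Up to nine clinical markers: HbA1c (Primary outcomes), and FBG, PBG, fasting insulin, C-peptide, insulin resistance index, IL-6, TNF-α and CRP (Secondary outcomes).
- 30 participants per group (Sample size).

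**Assumptions**
- 20 to 300 taxon tests in all.
- Every null hypothesis true.

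**Step 1: taxon comparisons.** The expected number of false positives is m × 0.05. The chance of at least one, if the tests are independent, is 1 − 0.95^m.

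| Taxon tests m | Expected false positives | Chance of at least one (independent) |
|---|---|---|
| 20 | 1.0 | 64% |
| 50 | 2.5 | 92% |
| 100 | 5.0 | 99.4% |
| 200 | 10 | over 99.9% |
| 300 | 15 | over 99.9% |

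**Step 2: dependence between taxa.** Taxa are not independent, and nested levels overlap by construction. A simulation of 30 versus 30 with 100 equally correlated, normally distributed taxa and no effect (2,000 runs per setting) gave:

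| Correlation between taxa | Mean false positives | At least one | Five or more |
|---|---|---|---|
| 0 | 5.0 | 99.5% | 57% |
| 0.3 | 5.1 | 94% | 37% |
| 0.6 | 5.0 | 64% | 26% |

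The average does not move. The certainty of seeing a false finding falls.

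**Step 3: correlations.** With nine markers:
- 20 taxa: 180 tests × 0.05 = 9 expected false correlations.
- 100 taxa: 900 × 0.05 = 45.
- 300 taxa: 2,700 × 0.05 = 135.

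If only HbA1c, FBG, PBG and the three inflammatory factors are meant, 100 taxa give 600 × 0.05 = 30.

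**Step 4: effect of the remedy.** In simulations with 50 to 200 taxa and correlations of 0 to 0.6, Benjamini-Hochberg at 5% lowered the chance of any false taxon finding from 51–100% to about 3–6%.

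**Step 5: a conditional point on pooling.** Suppose two variables are unrelated within each arm and treatment shifts them by d1 and d2 standard deviations. With 1:1 allocation, the correlation over both arms together is

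r = (d1·d2/4) / √[(1 + d1²/4)(1 + d2²/4)].

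- d1 = d2 = 0.8: 0.16/1.16 = 0.138.
- d1 = d2 = 1.0: 0.25/1.25 = 0.200.

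By Fisher's z with n = 60, these are significant in about 18% and 33% of trials. With 51 completers (60 × 0.85, the planned 15% drop-out), the figures are about 16% and 29%. The shifts are illustrative. Multiplicity control does not remove this effect; adjusting for arm does.

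**The case against.** The strongest reply is that the Statistical analysis section never names a taxon or correlation analysis. It lists t-tests, rank tests, covariance analysis and chi-square tests, and its last sentence may be a routine statement of sidedness and alpha. Sequencing analyses may have their own procedure in a document not shown. This stands in part: the application to taxa and correlations is inferred from the word *all*. But the sentence contains no exception, and microbiota abundance is a named secondary outcome, so a reader following the text would apply 0.05 to it.

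A second reply is that much of the article's language is exploratory. That is true of the Abstract, and it makes the repair easy. It does not remove the Background's stated purpose or the significance rule.

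A reader might also infer four stronger points that the document does not support.

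- *That the rule guarantees many false findings.* The number of taxa is nowhere given, the counts assume every null is true, and with strongly correlated taxa the chance of even one false finding among 100 falls to about 64%.
- *That taxa are tested at all five levels and each is correlated with every marker.* The article says abundance is calculated at five levels; it does not say at which level groups are compared or which taxa enter the correlations.
- *That the correlations pool the two arms.* The article does not say whether they are pooled, within arm or adjusted, so Step 5 is a caution and not a fault found.
- *That the eight other secondary outcomes also need adjustment.* If they were independent, the chance of at least one false positive would be 1 − 0.95^8 = 34%. They are not independent, since the insulin resistance index is built from fasting glucose and insulin. Leaving secondary outcomes unadjusted beside a single primary outcome is common and not an error in itself.

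**Conclusion.** The point holds in a limited form. As written, one unadjusted threshold governs every test, and nothing protects the taxon comparisons or the taxon-by-marker correlations from chance findings. On the assumed 20 to 300 taxon tests with no true effect, the expected yield is 1 to 15 false taxa; for 100 taxa and nine markers it is about 45 false correlations. These are averages under a global null and an assumed taxon count, and not predictions of what this trial will report.

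The primary conclusion on HbA1c is untouched, because it rests on one outcome and one between-group comparison at 12 weeks. What is at risk is the reading of the microbiota and mechanism results. The change should be made, but it does not threaten the trial's main result.

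**What to change.** 1. In Statistical analysis, restrict the closing sentence so that the unadjusted 0.05 rule does not apply to the microbiota and correlation analyses.
2. Add a sentence such as: *Between-group comparisons of taxa will be controlled at a 5% false discovery rate (Benjamini-Hochberg) within each taxonomic level, and correlations of abundance with clinical markers at a 5% false discovery rate within that family; these results are exploratory.*
3. In the last paragraph of the Background, replace *demonstrate* with *explore*.
4. If correlations are computed over both arms together, state that they are adjusted for arm, for example as partial correlations.

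If an unseen analysis plan already does this, the article's sentence only needs to be brought into line with it. The change should be fixed before the blind is broken.

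The cost is wording and a little programming, with no new patients or samples. Fewer taxa will be nominally significant. One limit remains: control within each of five levels allows up to 5 × 5% = 25% as an upper bound on any false taxon across all levels under a global null, so the exploratory label is still needed.
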